| 9. Subjects and numbers of subjects     | 
~ 1000 children 10-15 years of age for DENV and CHIKV seroprevalence study
 
~ 1000 parents of children from the seroprevalence study for a questionnaire study
 
~ 100 homes for mosquito sampling study
                                                                                                                                                                                                            |
| 10. Inclusion criteria                  | - Acceptance to participate                                                                                                                                                                                                                                                                                                                                                                                                           |
| 11. Exclusion criteria                  | - Refusal to participate or suffering from any concurrent infection or with any physical or mental disability.                                                                                                                                                                                                                                                                                                                        |
| 12. Material/ Biological samples        | 
- Finger-prick blood sample for use with Rapid Diagnostic Kit
 
- Adult mosquitoes
                                                                                                                                                                                                                                                                                                                                        |
| 13. Individual data collection and flow | 
For each participating child:
 
 
- information on age, sex and history of infection
 
- place of residence (longitude & latitude)
 
 
KAP questionnaire for parents/care givers – age, sex, address, education level
                                                                                                                                              |

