#### 4.3. Source of recruitment

Children of ages 10-15 years old from 8-12 schools will be invited to participate. The schools will be chosen from a list (below) based on their environmental and centrality typology.

| id_sch     | name                                                                              | type | nb_stu | class         |
|------------|-----------------------------------------------------------------------------------|------|--------|---------------|
| 3110023402 | โรงเรียนรัตนจินนุทิศ                                                              | BMA  | 420    | central-_env- |
| 3110015008 | โรงเรียนสุสันทองประดิษฐ์อนุสรณ์                                                   | BMA  | 152    | central-_env- |
| 10032003   | โรงเรียนสุวรรณพลับพลาพิทยาคม                                                      | OBEC | 671    | central-_env- |
| 3110010609 | โรงเรียนวัดธรรมมาภิรตาราม                                                         | BMA  | 133    | central-_env- |
| 3110012104 | โรงเรียนวัดนวลจันทร์                                                              | BMA  | 205    | central-_env- |
| 3110013706 | โรงเรียนคลองกลั่นต้น                                                              | BMA  | 173    | central-_env- |
| 10032029   | โรงเรียนแจรงฟอนวิทยา                                                              | OBEC | 411    | central-_env- |
| 10032012   | โรงเรียนนพรัตนพาราม                                                               | OBEC | 1200   | central-_env- |
| 3110014705 | โรงเรียนอานวยกนกศิโรตธิน                                                          | BMA  | 200    | central+_env+ |
| 3110013001 | โรงเรียนวัดราชสีห์ธาราม                                                           | BMA  | 110    | central+_env+ |
| 10032013   | โรงเรียนชีโนรสวิทยลัย                                                             | OBEC | 2079   | central+_env+ |
| 10032030   | โรงเรียนวัดบวรมงคล                                                                | OBEC | 400    | central+_env+ |
| 3110022710 | โรงเรียนวัดมะลิ                                                                   | BMA  | 176    | central+_env+ |
| 3110012003 | โรงเรียนเทพวิทยา                                                                  | BMA  | 217    | central+_env+ |
| 3110024503 | โรงเรียนสุเทพาภิวนดอน                                                             | BMA  | 106    | central+_env+ |

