### **5.1. General organisation of the study**

#### **A. Sero-prevalence**

A one-time cross-sectional sero-prevalence study to measure IgG seropositivity will be performed in each of the selected schools in pupils aged 10-15 years old. The total number of participants in the research project is 1000. Collected from 2-3 schools in each of the four area types.

After consent to allow child participation, the pediatrician will use a rapid diagnostic lateral flow blood test to measure the immunity against dengue and chikungunya from the children. The blood sampling will be drawn from the fingertips for two drops (1 drop per test) at the child school. The result will be reported within the same day of the test. Parents will be required to answer the Dengue and Chikungunya questionnaires.

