#### **C. Questionnaire**

A questionnaire about knowledge, attitude and practice about dengue infection, chikungunya infection, prevention, and control measure will be administered to the parents/care givers of the participating children (1000).

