Socio-demographic and other baseline characteristic variables of a questionnaire will be reported descriptively using counts and percentage for categorical variables and means for continuous variables. Comparison of willingness to be vaccinated and other associated factors will be performed using one-way analysis of variance. Multivariate regression analysis will be deployed to identify and understand the key factors that may be associated with the potential uptake a vaccine using generalized linear models.

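### The questionnaire analysis of parents' vaccine willingness and uptake makes no allowance for recruitment through 8-12 schools, so standard errors are too small for factors that vary mainly between schools and for intervals around overall percentages

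*Protocol*

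**What the plan says.** The protocol Summary (item 9) plans for about "1000 parents of children from the seroprevalence study for a questionnaire study". Section 5.1 C confirms that the respondents are the parents or care givers of the participating children. Those children come through schools. Section 4.3 states: "Children of ages 10-15 years old from 8-12 schools will be invited to participate". Section 5.1 A adds: "Collected from 2-3 schools in each of the four area types". Parents are therefore nested in schools, and schools in area types.

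The last paragraph of Section 9 gives the questionnaire analysis: "Comparison of willingness to be vaccinated and other associated factors will be performed using one-way analysis of variance". Multivariable regression is then to "identify and understand the key factors that may be associated with" "the potential uptake a vaccine using generalized linear models". No school term, random effect, GEE or robust variance is named, and the factors are not listed.

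Earlier in Section 9, the serology planning cites a coefficient of variation of 0.6-1 and uses it to set the number of schools per typology. Nothing comparable appears for the questionnaire.

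**The concern.** Parents of children at one school share a neighbourhood, a school population and often the same health messages. The Background section gives a reason to expect some school effect: in a cited KAP study, more than 70% of children named their teacher as their source of dengue information. That finding concerns children, but it makes a school component in household knowledge plausible.

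One-way ANOVA and generalized linear models, as named, assume independent observations. If parents within a school resemble each other, the information about anything that differs between schools comes from 8-12 schools, not from 1000 parents. Two outputs are at stake:

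- tests of factors that vary mainly between schools, where false positives could be reported as key factors for vaccine uptake;
- any interval around an overall KAP or willingness percentage. Section 5.3 says that the KAP data may inform public health campaigns.

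The serology model is a separate analysis with different respondents and outcomes, so a correction there would not by itself reach this one.

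**Working it through.** **Figure in the plan.** The protocol gives no sample size, power or ICC for the questionnaire. Its only computed sample size, about 210 per typology, belongs to the serology. With the printed constants it is (1.96 + 0.84)² × (0.26 × 0.74 + 0.15 × 0.85) / 0.11² = 7.84 × 0.3199 / 0.0121 = 207, which agrees. It does not bear on the questionnaire.

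**Inputs.** N = 1000 parents (Summary; Section 5.1 C). Schools: 8-12 (Section 4.3). Parents per school, m: 1000/12 = 83.3, 1000/10 = 100, 1000/8 = 125. ICC of the outcome: not in the document; 0.01, 0.02 and 0.05 are assumed.

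**Purely school-level factor, or an overall percentage.**
- Design effect DE = 1 + (m − 1) × ICC
- Ratio of true to naive standard error = √DE
- Effective sample = 1000 / DE
- Actual error rate of a nominal two-sided 5% test of a school-level factor = 2 × (1 − Φ(1.96/√DE))

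Example for 12 schools and ICC 0.01: DE = 1 + 82.3 × 0.01 = 1.82; √1.82 = 1.35; 1000/1.82 = 548; error rate 14.7%.

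| Schools (m) | ICC | DE | SE ratio | Effective N | Actual error rate |
|---|---|---|---|---|---|
| 12 (83.3) | 0.01 | 1.82 | 1.35 | 548 | 14.7% |
| 12 (83.3) | 0.02 | 2.65 | 1.63 | 378 | 22.8% |
| 12 (83.3) | 0.05 | 5.12 | 2.26 | 195 | 38.6% |
| 10 (100) | 0.01 | 1.99 | 1.41 | 503 | 16.5% |
| 10 (100) | 0.02 | 2.98 | 1.73 | 336 | 25.6% |
| 10 (100) | 0.05 | 5.95 | 2.44 | 168 | 42.2% |
| 8 (125) | 0.01 | 2.24 | 1.50 | 446 | 19.0% |
| 8 (125) | 0.02 | 3.48 | 1.87 | 287 | 29.3% |
| 8 (125) | 0.05 | 7.20 | 2.68 | 139 | 46.5% |

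An ICC of only 0.005 still gives a ratio of 1.19-1.27 and an error rate of about 10-12%. The 8-school rows assume that the total of 1000 is kept; at the 80-100 children per school given in Section 9, 8 schools would supply 640-800, and m would not exceed 100.

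**Few schools.** These error rates use a normal approximation and include no allowance for the small number of schools. A four-way area-type comparison would have only 8 − 4 = 4 to 12 − 4 = 8 degrees of freedom between schools.

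**Parent-level factor.** Here DE = 1 + (m − 1) × ICC(outcome) × ICC(factor). At m = 100 and a factor ICC of 0 to 0.1:
- factor ICC 0: ratio 1.00;
- factor ICC 0.05: ratios 1.02, 1.05 and 1.12 for outcome ICC 0.01, 0.02 and 0.05;
- factor ICC 0.1: ratios 1.05, 1.09 and 1.22.

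At 8 schools the last case becomes √(1 + 124 × 0.05 × 0.1) = √1.62 = 1.27.

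**The case against.** The strongest counter-argument is that the test most affected is not in the plan. Section 9 lists no school- or area-level factor for the questionnaire. Summary item 16 stratifies seroprevalence and mosquito abundance by typology, but not KAP. Section 7.2 describes a typology link for the serology and mosquito data; its KAP paragraph says only that the address is erased before analysis. The parent variables listed are age, sex, address and education level, and income is not among them. Section 9 also promises no interval for KAP or willingness percentages. All of this stands, and it makes the larger figures conditional.

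A reader might infer that the plan's vaccine-uptake results will carry a false-positive rate of 15-47%. The documents do not support that: the rate holds only for a purely school-level factor at an assumed ICC. A reader might also carry the serology coefficient of variation over to KAP. Through ICC = k²p/(1 − p) it would imply 0.36 × 0.15/0.85 = 0.064 (k = 0.6, p = 0.15) up to 0.26/0.74 = 0.351 (k = 1, p = 0.26). Nothing in the protocol links variation in infection to variation in parents' attitudes, so that transfer is not justified.

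A second argument is that variance estimation is usually left to the statistical analysis plan, which is not at hand, and that a generalized linear model can be fitted with GEE or a robust variance. This is fair for the generalized linear models. It is weaker for the ANOVA: a one-way analysis has no place for a school effect beside the factor compared, so the named method does not match the sampling design.

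**Conclusion.** The concern holds in conditional form. Run as written, the questionnaire analyses treat parents nested in 8-12 schools as independent. For a factor that varies only between schools, or an interval around an overall percentage, standard errors should be about 1.35-2.7 times larger. A nominal 5% test of such a factor would reject about 15-47% of the time. For parent-level factors such as age, sex and education, if they vary little between schools, the ratio is only about 1.00-1.22.

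This rests on an assumed ICC of 0.01-0.05, roughly equal school sizes and a total of 1000 parents; with an ICC of zero there is no inflation. The questionnaire serves a secondary objective. The point should be corrected, but it does not touch the primary serology result.

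**What to change.** In the questionnaire paragraph of Section 9:

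- Replace the one-way ANOVA with a regression that accounts for school: linear for composite scores, logistic for Yes/No items.
- Fit the generalized linear models for vaccine uptake with a school random intercept, or with GEE or cluster-robust variance. Any of these serves.
- State a correction for the small number of clusters, because 8-12 schools are too few for large-sample standard errors.
- Wherever KAP or willingness percentages are reported with intervals, make the intervals cluster-adjusted.
- Say whether any school- or area-level factor will be tested, since this decides how much the adjustment matters.

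The cost is a change of wording and somewhat wider intervals. No new data are needed: the participant code in Section 10.2 already contains the school number.

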## 10. REGLEMENTARY ASPECTS OF THE STUDY

**Typology:** Prospective analyses and Cross-sectional study

**Regulatory Framework:** Research must respect the Chulalongkorn University regulatory framework, international recommendations (Revised Declaration of Helsinki, 2013, CIOMS International Guidelines for Health-Related Human Behavioral Research, 2016) as well as the French regulations on data protection (Act N ° 78-17 relating to the protection of individuals with regard to the processing of personal data, 2016).

**Regulatory procedures:**

As a consequence of the regulatory framework mentioned above, it will be necessary to obtain:

- a favorable opinion from the Chulalongkorn University Committee of Ethics
- a favorable opinion from the IRB of the Institut Pasteur
- CNIL authorization in France if it does not comply with a reference methodology (conformity to be verified)
- there is no importing of human or mosquito biological samples or corresponding individual data into France.

### **10.1. Methods for information and consent for study participants**

The project will be explained to the children and a notice of information in Thai about the purposes of the study given to them and their parents. Recruitment will only occur once the parents / care givers have signed the written informed consent form and the children an assent form in the presence of an independent witness (school teachers).

### **10.2. Data confidentiality**

Once the RDT result and the grid level area of residence is established, the identification of the individual who provided the samples will no longer be possible. The identity of individual participants will be replaced with a code as follows:

Individual : XX-YYY-P/C

XX: School number

YYY: Individual number within the school

P/C: Parent or Child

Example: School 1, Individual 2, Child: 01-02-C

Correspondance between individual address and sample until geolocalisation enables environmental typology categorisation

### **10.3. Vigilance**

#### **Potential risks**

Risks from taking a finger-prick blood sample: bleeding, bruising, swelling at the site of the finger-prick, fainting. If any side-effects occur, seek medical attention from our doctors who will provide appropriate treatment. If associated symptoms are the result of this research project, treatment will be free of charge.

#### **Serious adverse event**

Any untoward medical occurrence, unintended disease or injury or any untoward clinical signs (including an abnormal laboratory finding) in subjects, users or other persons whether or not related to the procedures involved (any procedure in the clinical investigation plan).

An adverse event/reaction must be considered as serious when it:

- results in death,
- is life-threatening,
- requires hospitalisation or prolongation of existing hospitalisation
- results in persistent or significant disability or incapacity,
- is a congenital anomaly or birth defect,
- is medically important (Some medical events may jeopardise the subject or may require an intervention to prevent one of the above characteristics/consequences.).

Regarding a life- threatening event, this refers to an event in which the subject was at risk of death at the time of the event; it does not refer to an event which hypothetically might have caused death if it were more severe

The following events will not be considered as serious:

- A planned hospitalization for pre-existing condition, or a study-specific procedure described in the protocol, without a serious deterioration in health
- Hospitalisation for a duration less than 24 h (i.e. not requiring a night in the hospital), unless it could be considered as an important medical event,
- Hospitalisations which have been planned before the subject's participation in the protocol,
- Hospitalisation for the treatment of a concomitant pathology diagnosed before the subject's participation in the protocol, except if the treatment intensity or frequency is increased during the subject's participation in the protocol,
- Hospitalisation for routine clinical procedures as well as on social grounds.

All serious adverse events experienced during the study, which are observed by the investigator or reported by the patient, will be recorded and declared to IRB.

#### **10.4. Insurance**

This project using a RDT is considered being at very low risk, but insurance is required.

### **12. DISSEMINATION OF THE RESULTS**

#### **12.1. Dissemination of the results to the participants**

Information concerning the results of this study will be communicated during a session at each of the schools to which the participating children and parents will be invited.

Individual communication to the patient of their results is planned as part of this study as the result from the rapid diagnostic test is instantaneous (a matter of minutes) and the child will still be present when the result is known.

#### **12.2. Rules for Publishing**

The results of the study may be published in scientific journals after validation by a reading committee, or presented at scientific or medical meetings or congresses. The rules of authorship will follow the international rules of the ICMJE. These publication arrangements may be supplemented by contractual means between the different participants in this research. Concerning collaborations with the various partners of the study, the list of signatories and people thanked in the articles to be submitted will be established after collegial discussion. Institut Pasteur and more particularly the Clinical Research Coordination Center must be mentioned as responsible for ethical-regulatory and operational research activities.

### 13. ARCHIVING

The following documents will be archived for 15 years following the completion of the project:

- Protocol signed by the research partners (an original kept with each of the partners and an original of all the partners with the initiator of the research)
- Observation book / data collection medium (original at the initiator of the research and copied to the investigators and / or other collaborators)
- Final report of the study

### 14. BUDGET

This project is financed by a French National Funding Agency (Agence Nationale de la Recherche) grant awarded to [name] and [name] for the Dengue RDT sero-survey and a Wellcome Trust grant to [name] for the mosquito collections [Total 2.2 million Thai Baht (56 000 euros)]. In addition, Chikungunya RDT sero-survey and Questionnaires study is supported by Ratchadapisek Sompoch Endowment Fund. [Total 400,000 Thai Baht]

